## Abstract

**Introduction:**

Herpes simplex virus (HSV) encephalitis is a rare severe form of brain inflammation that commonly leaves survivors and their families with devastating long-term consequences. The virus particularly targets the temporal lobe of the brain causing debilitating problems in memory, especially verbal memory. It is postulated that immunomodulation with the corticosteroid, dexamethasone, could improve outcomes by reducing brain swelling. However, there are concerns (so far not observed) that such immunosuppression might facilitate increased viral replication with resultant worsening of disease. A previous trail closed early because of slow recruitment.

**Method:**

DexEnceph is a pragmatic multicentre, randomised, controlled, open-label, observer-blind trial to determine whether adults with HSV encephalitis who receive dexamethasone alongside standard antiviral treatment with aciclovir for have improved clinical outcomes compared with those who receive standard treatment alone. Overall, 90 patients with HSV encephalitis are being recruited from a target of 45 recruiting sites; patients are randomised 1:1 to the dexamethasone or control arms of the study. The primary outcome measured is verbal memory as assessed by the Weschler Memory Scale fourth edition Auditory Memory Index at 26 weeks after randomisation. Secondary outcomes are measured up to 72 weeks include additional neuropsychological, clinical and functional outcomes as well as comparison of neuroimaging findings. Patient safety monitoring occurs throughout and includes the detection of HSV DNA in cerebrospinal fluid 2 weeks after randomisation, which is indicative of ongoing viral replication. Innovative methods are being used to ensure recrutiment targets are met for this rare disease.

**Discussion:**

DexEnceph aims to be the first completed randomised controlled trial of corticosteroid therapy in HSV encephalitis. The results will provide evidence for future practice in managing adults with the condition and has the potential to improve outcomes.

**Ethics and dissemination:**

The trial has ethical approval from the UK National Research Ethics Committee (Liverpool Central, REF: 15/NW/0545, 10 August 2015). Protocol V.2.1, July 2019. The results will be published and presented as soon as possible on completion.

**Trial registration numbers:**

ISRCTN11774734, EUDRACT 2015-001609-16.

Strengths and limitations of this studyDexEnceph will be the first completed randomised controlled trial of corticosteroids in herpes simplex virus encephalitis, examining the utility and safety.DexEnceph’s primary end point is verbal memory score recorded at 26 weeks after randomisation, this represents the most important neuropsychological damageThe recruitment target is informed by the recent Enceph-UK programme grant of encephalitis in the UK; the trial is currently open and has recruited 82 patients of a target 90.Innovative methods for engaging with recruitment sites have been key to ensuring the success of the study.

## Introduction

Herpes simplex virus infection (HSV) is the most commonly identified viral cause of encephalitis, inflammation and swelling of the brain caused by a virus or the body’s immune system, in the UK as in most western industrialised nations.^1–4^ The incidence has been estimated at 1 in 250 000–500 000,^2^ with evidence it may be higher.^4^ Although a rare disease, HSV encephalitis has a disproportionately large impact due to its devastating long term neuro-psychological sequelae. These can have a marked impact on the quality of life of the patient and their family and high health economic and social costs.^5 6^

Since the introduction of the antiviral drug aciclovir in the 1970s, the mortality of HSV encephalitis has reduced from around 70% to 5.5%–12%.^7–9^ However, survivors are commonly left with neurological impairment; less than 20% of patients are able to return to work and 48% are classed as moderate to severely disabled.^10^ Even when obvious disabilities have not occurred, families often report personality changes—the person they take home from hospital is simply not the same as the one before the illness.^6 11^

HSV encephalitis can cause a broad range of cognitive impairments, but impaired memory, especially verbal memory, is the most common and likely relates to the viral predilection for the temporal lobe of the brain.^12 13^ The verbal memory deficits manifest as difficulties remembering names of objects and people, as well as listening to and recalling spoken information for example in conversations.^14 15^ In addition to memory problems, difficulties in processing speed, concentration, language and executive function are also common among survivors of HSV encephalitis, along with fatigue, poor concentration, anxiety and depression.^7 16 17^

The pathogenic mechanisms in HSV encephalitis are not fully understood. The evidence suggests that in addition to direct viral pathogenesis, inflammation of the brain in response to the virus is a key component of the disease process.^18–21^ This is supported by the observation that in the cerebrospinal fluid (CSF), higher levels of proinflammatory chemokines, especially monocyte chemotactic protein-1, interferon γ and interleukin 6 (IL-6) are associated with a worse prognosis.^22 23^ Poor prognosis is also associated with the extent of inflammation seen on neuroimaging,^24^ and the degree of temporal lobe swelling is correlated with the severity of verbal memory impairment.^25^ Relapse occurs in about approximately 10% of HSV encephalitis patients, and is sometimes associated with the development of anti-N-Methyl-D Aspartic acid (NMDA) antibodies.^26^

Control of the inflammation in HSV encephalitis may improve outcome, as shown in mouse models of the disease.^27–29^ Before the availability of aciclovir, corticosteroids were sometimes used as a treatment in humans with HSV encephalitis,^30 31^ and more recently both cerebral oedema on imaging and CSF IL-6 levels were shown to be reduced in patients given corticosteroids.^23^ However, because corticosteroids cause immunosuppression, which in theory facilitates increased viral replication, their role is uncertain.^32^

In other brain infections, including bacterial meningitis and tuberculous meningitis the benefit of corticosteroids has been demonstrated in large clinical trials.^33^ For HSV encephalitis the potential benefit of using corticosteroid as an adjunct to aciclovir therapy has been suggested from small case series and retrospective comparisons, but there has been no prospective randomised study reported.^34–39^ One study, the German trial of Aciclovir and Corticosteroids in Herpes simplex virus Encephalitis (the GACHE trial) was stopped early because of poor recruitment rates.^40^ However, there is clearly a need for a study to answer this question. The DexEnceph Study, a randomised controlled trial of dexamethasone in HSV encephalitis, aims to achieve this.

### Trial design

DexEnceph is a pragmatic, multicentre, randomised, controlled, observer-blind trial to determine whether the addition of dexamethasone to standard aciclovir treatment improves clinical outcomes (in particular verbal memory score) for adults with HSV encephalitis. Additionally, neuroimaging and biomarkers are assessed along with detection of HSV in the CSF at 2 weeks after randomisation to monitor for difference in viral replication between the two groups.

### Primary objective

To determine whether a short course of intravenous dexamethasone, in addition to standard care, improves verbal memory score in adults with HSV encephalitis at 26 weeks after treatment compared with standard care alone.

### Secondary objectives

Secondary objectives include the following:

To determine whether dexamethasone therapy has an effect on other neuropsychological, cognitive, clinical, disability and functional outcomes in HSV encephalitis.

To assess the effect of dexamethasone therapy on brain swelling examined by neuroimaging.

To determine whether dexamethasone therapy affects clearance of HSV from the CSF, the emergence of NMDA receptor antibody or causes any changes in transcriptomic and proteomic profiling in the CSF and blood.

A more comprehensive list of measures is detailed in the outcomes section.

## Methods and analysis

DexEnceph is an observer-blind, open-label, prospective, randomised, controlled trial of dexamethasone at 10 mg four times daily for 4 days, versus no dexamethasone, in adults with HSV encephalitis.

### Research setting

The trial is being conducted in up to 45 National Health Service (NHS) trusts, with a recruitment target of 0–2 patients per site per year. A full list of sites involved in DexEnceph can be obtained from www.dexenceph.org.uk. The trail uses Standard Protocol Items: Recommendations for Interventional Trials reporting guidelines^41^ (online supplemental file 1).

10.1136/bmjopen-2020-041808.supp1Supplementary data

### Eligibility criteria

#### Inclusion criteria

Enrolled patients fulfil all of the following criteria:

Suspected encephalitis defined as: new-onset seizure or new focal neurological signs or alteration in consciousness, cognition, personality or behaviour. Personality/behavioural change includes agitation, psychosis, somnolence, insomnia, catatonia, mood lability, and altered sleep pattern.A positive HSV DNA PCR result from CSF, reported not more than 7 days prior to randomisation.Receiving intravenous aciclovir administered as 10 mg/kg three times daily or at a reduced dose if clinically indicated.Age≥16 years.Written informed consent given by the patient or their legal representative^42^

#### Exclusion criteria

Patients are excluded if they have any of the following:

Have received oral or injectable corticosteroid therapy in the 30 days prior to the day of entry to the study. This does not apply to topical/ inhaled corticosteroids. (Patients who have received oral or injectable corticosteroid therapy AFTER their admission to hospital will not be excluded from the study if they consent to trial participation).History of hypersensitivity to corticosteroids.Immunosuppression secondary to:Known HIV infection and CD4 white cell count under 200/mm^3.^Currently taking biological therapy or other immunosuppressive agents (eg, azathioprine, methotrexate, ciclosporin)Previous solid organ transplant and currently on immunosuppression.Previous bone marrow transplant.Currently undergoing a course of chemotherapy or radiotherapy.Known primary immunodeficiency syndrome.Known current haematological malignancy.Pre-existing indwelling ventricular devices.Peptic ulcer disease in the last 6 months, defined as a peptic ulcer seen at endoscopy or an upper gastrointestinal bleed causing a ≥2 unit haemoglobin drop, in the last 6 months.Antiretroviral regimen containing rilpivirine as current treatment (levels of rilpivirne are known to significantly decrease in coadministration with dexamethasone, a switch to a suitable alternative can facilitate trial entry).

### Intervention

Participants are randomised in a 1:1 ratio to dexamethasone four times daily for 4 days alongside standard care, or standard care alone (figure 1). Standard care includes intravenous aciclovir for a minimum of 14 days based on an ideal body weight at 10 mg/kg every 8 hours, unless dose adjustment to account for renal impairment is necessary. Participating clinicians remain free to modify or discontinue the dexamethasone administration or to give alternative treatments at any stage, if this is judged to be in the best interest of the patient.

**Figure 1 F1:**
[figure not shown]
Schematic design of DexEnceph randomised controlled trial.

Participants assigned dexamethasone receive 10 mg equivalent of ordinary ward stock, prescribed by an authorised member of the local study team, given intravenously four times daily for 4 days (16 doses in total) starting within 24 hours of randomisation.

The University of Liverpool employs a clinical trials unit to be responsible for screening, and monitoring data collection, quality and completeness. As there is a low number of participants to be recruited, the trials unit are able to liaise regularly with each site following randomisation to ensure all follow-up data are collected. Primary outcome is recorded by a centrally employed roving neuropsychologist, who collects the neuropsychological outcomes at 26 and 72 weeks.

### Outcome measures

#### Primary outcome

Verbal memory score, determined by the Wechsler Memory Scale fourth edition (WMS-IV) Auditory Memory Index, at 26 weeks after randomisation. Patients that die will be allocated the lowest possible WMS-IV score.

### Secondary outcomes

Other neuropsychological outcome measures (at 26 weeks and 78 weeks after randomisation):

Verbal memory score, determined by the WMS-IV, Auditory Memory Index, at 78 weeks after randomisation.Visual, Immediate and Delayed Memory by Indexes of the WMS-IV, processing speed and working memory subscales from the Wechsler Adult Intelligence Scale Fourth Edition.Higher executive function using the Trail Making Test.Anxiety and Depression symptom levels by the Beck Depression Inventory and Beck Anxiety Inventory.Subjective cognitive complaints using the Perceived Deficits Questionnaire.

Cognitive Outcome Measures (at discharge or 30 days if still in hospital, 26 weeks and 78 weeks).

Addenbrooke’s Cognitive Assessment III.

### Clinical Outcomes

Incidence of epilepsy.Time to hospital discharge.Requirement of high-dependency unit or intensive care unit admission up to 30 days after randomisation.Time taken to be free of ventilatory support for 14 days (if any).Time to reach maximum recorded Glasgow Coma Scale score.Survival.

Disability and functional outcomes (at discharge or 30 days if still in hospital, 26 weeks and 78 weeks):

Modified Rankin Score, Barthel Index, Liverpool Outcome Score and Glasgow Outcome Scale Extended.

Imaging Outcomes: Change from Baseline at 2 weeks, 26 weeks and 78 weeks

Temporal lobe volume (as percentage of intracranial volume).Whole brain volume (as percentage of intracranial volume).Volume of affected region as seen on fluid-attenuated inversion recovery image (as percentage of intracranial volume).Volume of affected region as seen on diffusion-weighted image (as percentage of intracranial volume).

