### Participant timeline

The time schedule for enrolment, interventions and assessments is given in table 1.

**Table 1 T1:** Time scale for patients randomised in the DexEnceph study

Procedures	Inntervention and follow-up schedule						
	Screening	Baseline	2 weeks	Discharge or day 30 of admission (whichever is sooner)	26 weeks	78 weeks	Premature discontinuation
Signed consent form	X*	X†					
Assessment of eligibility criteria	X	X†					
Review of medical history		X†					
Review of concomitant medications		X†	X	X	X	X	X
Physical exam		X		X			
Study intervention		X					
Clinical data collection		X		X	X	X	
MRI scan		X‡	X		X	X	
Research blood testing		X	X		X		
Lumbar puncture		X§	X				
Disability and functional outcomes				X	X	X	
Glasgow Coma Scale		X¶†	X¶	X¶	X	X	
Addenbrooke’s cognitive examination				X	X	X	
Neuropsychology assessment, including verbal memory score					X	X	
Health status and quality of life questionnaires					X	X	
Clinical laboratory: haematology, biochemistry		X**					
Assessment of adverse events			(X)	(X)	(X)	(X)	(X)

(X)—As indicated/appropriate.

*Only applicable when patients are prospectively consented for the randomised controlled trial.

†Procedures required before randomisation.

‡Baseline MRI done for clinical purposes can be done from hospital admission up to 7 days after randomisation.

§Diagnostic lumbar puncture for clinical purposes done prior to randomisation.

¶Recorded prior to randomisation, daily for the first 14 days and then weekly until discharge/30 days (whichever sooner).

**Recording of clinic al laboratory tests done for clinical purposes, not as part of trial.

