### Statistical considerations

#### Sample size

The primary outcome variable is verbal memory, assessed as part of WMS-IV. In one published series of adults who survived HSV encephalitis, 19 of 22 had memory impairment evident at follow-up, with verbal memory being most severely affected.^12^ In that study the mean (SD) verbal memory score was 88.9 (18.9) compared with the population mean (SD) of 100.^15^ This score can only be assessed in survivors, we estimate approximately 10% of patients in the trial will die before assessment of the primary outcome.^8 43 44^ In instances where the death is judged to be associated with encephalitis the verbal memory score is recorded as 40, (the lowest possible value which would be obtained even where a patient recorded no recall of any of the items administered in the memory subtests). Where the cause of death is thought to be independent of having encephalitis, those patients will be recorded as lost to follow-up. Similarly, for patients who are too unwell, due to encephalitis, to undergo the assessment, the score is recorded as 40. Decisions as to whether the reasons for death or non-completion of the measures were due to encephalitis will be made by an independent committee blinded to dexamethasone allocation. Adjusting the estimate of mean and SD from survivors, to include the 10% of patients that die having the lowest possible value of 40, gives a total population mean of 84.8, with a SD of 23.1. A final sample size of 36 participants per group allows us to detect a clinically meaningful difference of 15.5 on the verbal memory score with 80% power, at a two-sided significance level of 0.05. Allowing for up to 20% dropout gives an initial target sample size of 45 participants per group, for a total of 90.

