### Statistical analysis

For the primary outcome, participants are included in the analysis based on the intention-to-treat principle. Verbal memory score will be compared between groups using linear regression. The model will be adjusted for prespecified variables which are judged to be potentially related to the outcome, including age and admission Glasgow Coma Scale Score. No interim analysis is planned, but there is regular monitoring by the IDSMC.

As there may be some missing primary outcome data due to death, inability to complete the assessment, or loss to follow-up, a sensitivity analysis will be carried out. All randomised patients will be included in this analysis.

For continuous secondary outcome variables, comparisons between groups will be analysed as per the primary outcome. The results for residual viral presence in the CSF at 2 weeks will be reported with a 95% CI for the difference in proportions between groups. Time to event outcomes will be analysed using Kaplan-Meier curves, log rank tests and Cox proportional hazards models. Binary secondary outcomes will be analysed using logistic regression.

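### Timing each patient to their own highest recorded GCS gives the shortest times to those who decline or plateau low, so this secondary comparison can be diluted or reversed

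*Protocol article*

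**What the plan says.** The protocol article, under Clinical Outcomes, lists "Time to reach maximum recorded Glasgow Coma Scale score" among the secondary outcomes. No target score is attached to it.

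The Table 1 footnote in Participant timeline gives the in-hospital GCS schedule: "Recorded prior to randomisation, daily for the first 14 days and then weekly until discharge/30 days (whichever sooner". Table 1 also marks GCS at 26 and 78 weeks. The article does not say whether those late readings, or the pre-randomisation reading, count towards the maximum.

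Under Statistical analysis: "Time to event outcomes will be analysed using Kaplan-Meier curves, log rank tests and Cox proportional hazards models". No rule for death, deterioration or failure to improve is given for the GCS outcome. The one worst-score rule for death, "Patients that die will be allocated the lowest possible WMS-IV score" (Primary outcome, qualified under Sample size), concerns verbal memory only. Deaths will not be rare: "we estimate approximately 10% of patients in the trial will die before assessment of the primary outcome" (Sample size).

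**The concern.** A time-to-event outcome for recovery should give short times to patients who do well and leave patients who do badly without the event. Here the event is defined relative to the patient's own course. A patient whose first score is their best has had the event at once, whether that score was 15 or 9 and whether they then stayed level, worsened or died. A patient who keeps improving has the event late, because the maximum keeps moving. Every patient with at least one recorded score has an event, so non-recovery never appears as censoring or as a failure.

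The risk is a published hazard ratio for recovery of consciousness that is pulled towards no effect, or points the wrong way, when the drug increases the number of patients who recover.

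**Working it through.** **Plan's own figure.** The article states no figure for this outcome. The illustration below uses its trial size: 36 per group / 0.8 = 45 per group, randomised 1:1.

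**Step 1: apply the definition.** As written, T = the first t at which GCS(t) equals the patient's highest recorded score, and the event indicator is always 1. With a fixed target, T* = the first t at which GCS reaches 15, with no event if 15 is not reached by day 30. Four constructed courses, read at days 0 to 14, 21 and 28:

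| Course | T as written | T as written, pre-randomisation score excluded | T* (GCS 15) |
|---|---|---|---|
| Steady decline from 13 to 3 | day 0 | day 1 | not reached |
| Plateau at 9 | day 0 | day 1 | not reached |
| Partial recovery, 9 to 11 | day 4 | day 4 | not reached |
| Full recovery, 9 to 15 | day 10 | day 10 | day 10 |

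The two worst courses have the shortest times. Excluding the pre-randomisation score moves them by one day and leaves the order unchanged. This step needs no assumed rates.

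**Step 2: effect on mean times.** All rates here are assumptions; the article gives none for GCS recovery.
- Control: 10% decline early, 30% plateau low, 60% reach 15. Dexamethasone: 5%, 15%, 80%.
- Decliners' time is uniform on 0 to 1 day (mean 0.5). Plateau patients' time is exponential with mean 3 days.
- Recoverers' time is exponential with median m, capped at 30 days, so its mean is (m / ln 2) × (1 − 2^(−30/m)).
 - m = 8: 11.54 × (1 − 0.0743) = 10.68 days
 - m = 6: 8.66 × (1 − 0.0313) = 8.39 days
 - m = 5: 7.21 × (1 − 0.0156) = 7.10 days

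Mean time to own maximum:
- Control, m = 8: 0.10 × 0.5 + 0.30 × 3 + 0.60 × 10.68 = 7.36 days
- Dexamethasone, m = 8: 0.05 × 0.5 + 0.15 × 3 + 0.80 × 10.68 = 9.02 days
- Dexamethasone, m = 6: 0.475 + 0.80 × 8.39 = 7.18 days
- Dexamethasone, m = 5: 0.475 + 0.80 × 7.10 = 6.16 days

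Simulated medians at 200,000 per arm are 4.05 days for control, and 5.92, 4.64 and about 4.0 days for dexamethasone at m = 8, 6 and 5. With equal speed, the arm with 20 percentage points more full recovery looks slower. At m = 6 the means are nearly equal and the treated median is still longer. At m = 5 the medians are about equal and the mean favours dexamethasone.

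**Step 3: what a trial of 45 per arm would report.** Two-sided log rank test at 0.05, same assumptions:

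| Treated recoverers' median (control 8 days) | As written: significant harm | As written: significant benefit | Fixed target, non-recoverers at risk to day 30: significant benefit |
|---|---|---|---|
| 8 days | about 14% | about 0% | about 41% |
| 6 days | about 2% | about 4% | about 68% |

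Repeat runs differ by up to about 3 percentage points. In the second row the outcome as written behaves almost as if there were no treatment effect, although the assumed drug improves both the proportion recovering and their speed.

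**Step 4: a starker set of assumptions.** Suppose non-recoverers never exceed their baseline score and recoverers reach 15 between days 4 and 14 at the same speed in both arms. With full recovery of 60% v 75%, 50% v 70%, 40% v 70% and 75% v 90%, significant apparent harm as written occurs in 12% to 46% of trials. Significant benefit with the fixed target occurs in 30% to 80%. These runs allow no gain in speed, so they sit at the unfavourable end.

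**The case against.** **The reversal rests on chosen assumptions.** This stands. Equal recovery speed removes the effect the outcome is presumably meant to capture. If dexamethasone only speeds recovery in patients who would recover anyway, the direction is correct. The assumed 40% v 20% failing to reach 15 have no source in the article. The eligibility criteria set no GCS limit, so some patients may enter at or near 15, and the illustration includes none of them.

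**A reader might infer that the outcome will show a helpful drug as harmful.** The article does not support that. At the trial's size, significant apparent harm is a minority result even in the first scenario and nearly vanishes in the second. Nor should the ratio of mean times in the first scenario, 7.36 / 9.02 = 0.82, be read as the hazard ratio the trial would report.

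**The full protocol or analysis plan may say how death and the baseline score are handled.** That is possible, and their absence from an article is not a fault. But the event itself is stated here. A death rule would not change the result for a surviving patient who plateaus low.

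**Maximum may mean the scale maximum of 15.** The word "recorded" points to the patient's own maximum. If 15 is meant, the text should say so.

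**Survival, high-dependency or intensive care admission and four disability scales are reported alongside.** They limit how far a misleading result would be believed, but they do not change how this outcome is scored.

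**Conclusion.** Wrong as written, for one secondary outcome. That the worst courses receive the shortest times follows from the definition and the recording schedule alone. The consequence is conditional: dilution or reversal if treatment converts non-improvers into recoverers, and the correct direction if it only accelerates recovery. The sizes quoted rest on assumed recovery shares and speeds and show what can happen, not what will. The more robust result is the loss of information: under the same assumptions, a fixed target detects benefit far more often than the outcome as written. The primary outcome, its analysis and the sample size are not affected.

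**What to change.** Redefine the outcome as time from randomisation to first reaching a prespecified fixed GCS level, for example 15.
- Keep patients who have not reached it at risk to day 30, and treat death before reaching it as a competing event.
- Count patients discharged at the target level as having reached it, and state a rule for those discharged below it, because the in-hospital series stops at discharge.
- Report patients already at the target at randomisation separately.
- Do not require a second confirming reading, or let discharge at the target level serve as confirmation. Readings are weekly after day 14 and stop at discharge or day 30, so a two-reading rule would count some early-discharged or late recoverers as not recovered.

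The cost is a redefinition using GCS data already collected, with no new visits or patients. It should be documented before the arms are compared on this outcome. The downsides are that patients already at the target do not contribute and that timing after day 14 is known only to the week.
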